## Abstract

**Background:**

Cancer Care Ontario’s Screening Activity Report (SAR) is an online audit and feedback tool designed to help primary care physicians in Ontario, Canada, identify patients who are overdue for cancer screening or have abnormal results requiring follow-up. Use of the SAR is associated with increased screening rates. To encourage SAR use, Cancer Care Ontario sends monthly emails to registered primary care physicians announcing that updated data are available. However, analytics reveal that 50% of email recipients do not open the email and less than 7% click the embedded link to log in to their report.

**Objective:**

The goal of the study is to determine whether rewritten emails result in increased log-ins. This manuscript describes how different user- and theory-informed messages intended to improve the impact of the monthly emails will be experimentally tested and how a process evaluation will explore why and how any effects observed were (or were not) achieved.

**Methods:**

A user-centered approach was used to rewrite the content of the monthly email, including messages operationalizing 3 behavior change techniques: anticipated regret, material incentive (behavior), and problem solving. A pragmatic, 2x2x2 factorial experiment within a multiphase optimization strategy will test the redesigned emails with an embedded qualitative process evaluation to understand how and why the emails may or may not have worked. Trial outcomes will be ascertained using routinely collected administrative data. Physicians will be recruited for semistructured interviews using convenience and snowball sampling.

**Results:**

As of April 2017, 5576 primary care physicians across the province of Ontario, Canada, had voluntarily registered for the SAR, and in so doing, signed up to receive the monthly email updates. From May to August 2017 participants received the redesigned monthly emails with content specific to their allocated experimental condition prompting use of the SAR. We have not yet begun analyses.

**Conclusions:**

This study will inform how to communicate effectively with primary care providers by email and identify which behavior change techniques tested are most effective at encouraging engagement with an audit and feedback report.

**Trial Registration:**

ClinicalTrials.gov NCT03124316; https://clinicaltrials.gov/ct2/show/NCT03124316 (Archived by WebCite at http://www.webcitation.org/6w2MqDWGu)

## Introduction

Health care provider behavior is an important determinant of patients’ use of screening services [1-5]. A number of knowledge translation strategies intended to target provider behavior already exist **,** including audit and feedback [6], reminder/recall systems [7], and incentives [8]. The effectiveness of these strategies varies considerably and may be partly explained by variation in the features of the interventions [6,7], the differing clinical contexts in which the interventions are used, and the extent to which clinicians actually engage with the interventions [9,10]. For example, physicians may not access feedback reports regularly if they lack trust in data quality, if they are not motivated to improve on the indicators measured, or if they encounter organizational or other constraints that interfere with quality improvement [11].

In 2012, the global burden of cancer amounted to 8.2 million deaths, representing 13% of all deaths globally [12,13]. Screening can reduce cancer-related mortality [14] if appropriate tests are used [15] and if a sufficient number of patients from the target population participate [16]. Despite the availability of organized screening programs for colon, breast, and cervical cancer in Ontario, Canada [17], more than one-third of the eligible population in the province are not up to date with screening tests for these cancers [18].

Cancer Care Ontario (CCO) is the agency that oversees population-based cancer screening programs in Ontario. It currently uses a multifaceted strategy to increase cancer screening rates, including public media campaigns, letters mailed to patients overdue for screening, and an audit and feedback tool available to primary care physicians. The online audit and feedback tool, known as the Screening Activity Report (SAR), is updated monthly to help primary care providers identify specific patients who are overdue for screening and/or who have screening results that require follow-up in addition to comparing their performance to the regional average. Use of the SAR by primary care physicians is associated with higher rates of colorectal, breast and cervical screening [19]. However, most primary care physicians in the province do not regularly use the SAR. To encourage use, CCO sends a monthly email to primary care physicians who have registered for the SAR (see Multimedia Appendix 1); however, internal CCO data extracted in 2016 revealed that 50% of email recipients did not open the email, and less than 7% of recipients clicked the enclosed link to log in to their SAR. Therefore, we worked with CCO to develop a study to test theory- and user-informed content to improve the salience and impact of emails, with the objective of increasing SAR access and, ultimately, aligning cancer screening rates with guidelines. In this manuscript, we describe the design of a pragmatic, factorial randomized experiment using the Multiphase Optimization Strategy (MOST) [20] to evaluate the impact of different components in the monthly SAR delivered by email to primary care physicians across Ontario and an accompanying process evaluation.

## Methods

### Intervention Design: Monthly Emails Prompting Use of the Screening Activity Report

The team first employed a user-centered design approach informed by principles of behavior change theory to rewrite the monthly emails and identify email components, or behavior change techniques (BCTs), to test in an experiment . BCTs are defined as “active components of an intervention designed to change behavior” [21]. We identified BCTs from the Behavior Change Technique Taxonomy (v1) [22] that could influence primary care physician behavior [23].

The rewriting process emphasized content development and involved focus groups with adopters (physicians who already access and use the SAR) and nonadopters (physicians who have not accessed the SAR for at least 1 year). CB and DL, both qualitative experts at Cancer Care Ontario, led the groups of discussion. Through this process, we identified 3 modifiable components that could be prioritized for testing in a trial. Specifically, we hypothesized that the following BCTs could help increase the effectiveness of the emails: anticipated regret (ie, induce or raise awareness of expectations of future regret about not logging in to the SAR), material incentive (behavior) (ie, Identify opportunity for using SAR to access available monetary bonus for achieving high cancer screening rates ), and problem solving (ie, generate or select strategies that include overcoming barriers and/or increasing facilitators to accessing the SAR) (see Multimedia Appendix 2). The details of this process and the iterative changes made based on adopter input will be reported separately.

The BCTs tested are presumed to target 1 or more determinants of behavior (ie, the potential mechanism of action) as described in the theoretical domains framework (Table 1).

We verified the importance of the selected BCTs with adopters and nonadopters. We used the theoretical domains framework terminology to describe the potentially relevant determinants because mapping between BCTs and theoretical domains framework is already established [21,24]. For example, “anticipated regret” targets emotion and beliefs about consequences, which may drive primary care physicians to access their SAR (Figure 1).

### Study Design

This approach follows the MOST framework to optimize and evaluate multicomponent behavioral interventions [20,25]. Factorial experiments allow for the estimation of main effects of multiple factors in a single experiment by combining experimental conditions [26,27]. Thus, such designs are useful options in health behavior research to efficiently compare more than 1 intervention, particularly, as in our case, when there is no expectation that the factors being tested will substantially interact [28,29]. The trial itself is a 2×2×2 factorial randomized experiment with 8 experimental conditions (Figure 2). 

**Table 1 table1:** Content and hypothesized mechanism of change for each behavior change technique.

Items	Behavior change techniques/factors tested		
	Material incentive (behavior)	Anticipated regret	Problem solving
General description^a^	Explicitly link SAR^b^ use to a monetary bonus^c^ (awarded only if achieving high cancer screening rates)	Induce or raise awareness of expectations of future regret about not logging in to the SAR	Provide strategies that aim to overcome identified barriers to accessing the SAR
Operationalization	Logging into the SAR can help you maximize your screening rates and save time when calculating your preventive care bonus.	How would you feel if a patient had a poor outcome because you missed an abnormal test result?	We know accessing the SAR involves work for you and your staff. Here are 3 tips from other Ontario primary care doctors on how to fit using the SAR into your schedule: Email ONE ID at [contact] to register a delegate with eHealth Ontario so they can check your report Book calendar time right now to check your report Tackle a few patients at a time
Theoretical domains framework-based determinants	Reinforcement, intention	Emotions, beliefs about consequences, intention	Behavioral regulation, environmental context and resources

^a^The descriptions of the behavior change techniques are in line with the Behavior Change Techniques Taxonomy (v1) [22].

^b^SAR: Screening Activity Report.

^c^The financial incentive was already available from the Ministry of Health for achieving screening thresholds; the communication emphasizes how use of the SAR can help in attaining the bonus funds associated with these thresholds.

**Figure 1 figure1:**
[figure not shown]
Logic model of the content and hypothesised mechanism of change.

**Figure 2 figure2:**
[figure not shown]
Allocation flow diagram.

Three components in the redesigned SAR email will be tested. Each of these 3 factors in the trial will either be turned on or turned off in the email (Table 2).

The trial received approval from the Research Ethics Board at Women’s College Hospital and is registered on ClinicalTrials.gov [NCT03124316].

### Setting

The setting for this study will be primary care because this is the main point of entry to the health care system for Ontarians. In Ontario, the vast majority of primary care is delivered by primary care physicians, and patient visits to physicians are covered under the provincial health plan. According to Statistics Canada, 92.5% of Ontarians aged 12 years and over have a regular medical doctor, usually a primary care physician [30]. Almost three-quarters (73%) of Ontarians are associated with a primary care physician working in a physician enrollment model, meaning the primary care physician has an identifiable list of patients [31]. Primary care physicians working in physician enrollment models can register for the SAR and thus automatically receive the monthly email update from CCO.

### Participants and Recruitment

Eligible participants will be primary care physicians already registered to access the SAR and receive monthly emails from CCO. In Ontario, as of May 1, 2017, 8462 primary care physicians were working in a patient enrollment model. Of these, 5576 eligible physicians had signed up for the SAR. These 5576 physicians will be automatically enrolled in our study. We received a waiver of consent for providers’ participation because the intervention (email receipt) was considered to pose minimal risk (as primary care physicians were already receiving an email), individual primary care physician recruitment was not feasible, and there were concerns that informing providers about the trial might prime participants to act in a certain manner. Participating physicians can opt out of receiving the SAR emails as usual.

### Allocation and Blinding

A deidentified list of eligible participants will be exported from CCO to an independent statistician who will allocate participants to receive 1 of the 8 experimental conditions via simple randomization using computer-generated random numbers.

The different email versions (featuring the different BCTs to be tested) (see Multimedia Appendix 3) will be sent out in 45-minute intervals starting from 9 AM on the 10th day of each month (or if the day falls on the weekend, on the next business day) for 4 months between May and August 2017. The emails could not be sent at the same time since the Cancer Care Ontario’s outgoing mail server could not handle sending out all of the emails at the same time. That is why a delivery schedule made up of 9 intervals (each 45 minutes long) was devised. To address the concern raised regarding sending time, we randomized the order in which the email versions would be sent (ie, 1 version sent per interval) per month. Delivery order will be determined via block randomization. 

**Table 2 table2:** Experimental conditions. + refers to the presence of the factor and – refers to the absence of the factor.

Experimental condition	Factor 1: anticipated regret	Factor 2: material incentive	Factor 3: problem solving
1	–	–	–
2	+	–	–
3	–	+	–
4	–	–	+
5	+	+	–
6	+	–	+
7	–	+	+
8	+	+	+

All randomization procedures will be conducted in SAS version 9.4 (SAS Institute Inc). Treatment allocation will be concealed from the research team and CCO collaborators. It is not possible to blind participants as they must receive the intervention and may notice differences in email content and design; however, they are unlikely to be aware of the different components of the email being tested.

### Data Collection and Outcomes

In this experiment, all data will be routinely collected from CCO administrative databases. Table 3 details the variables to be collected and used in analysis.

All outcomes will be measured at the level of the physician-participant. The primary outcome will be a dichotomous variable indicating whether or not the primary care physician accessed the SAR at least once between May and August 2017. Secondary outcomes measured at the end of the 4-month trial via CCO database sources will be the total number of times the SAR was accessed (between May and August 2017) and physician adherence to screening guidelines for breast, colon, and cervical cancer for their practice (as of August 31). Process measures will include the number of participants opting out of emails or with emails that bounce back (ie, inactive email address) and the number of calls to CCO and/or eHealth Ontario contact center during the trial regarding the SAR (eg, password retrieval queries).

### Statistical Analyses

Physician baseline characteristics (sex, years of practice), their history of SAR use (previous use/no previous use), their baseline cancer screening rates (breast, cervical, and colon), and their practice characteristics (size of group, rurality, payment model) will be described across experimental conditions.

The unit of analysis for all outcomes will be the primary care physician. The effect of each intervention factor on the primary outcome (accessing the SAR at least once during the 4-month trial) will be analyzed using logistic regression. Indicator variables will be specified for each of the experimental factors using effect coding where +1 indicates the presence and –1 the absence of each factor. With effect coding, the regression coefficient represents the difference in the mean response across all experimental conditions with that factor turned on against the mean for all experimental conditions with that factor turned off. For example, the regression coefficient for “anticipated regret” will represent the difference in the log-odds of accessing the SAR for providers allocated to conditions where this factor is turned on (study arms 2+5+6+8) versus providers allocated conditions where the factor is turned off (study arms 1+3+4+7) (Table 2). The effect of each intervention factor will be expressed as an odds ratio with 95% confidence interval. The model will adjust for history of SAR use as a fixed covariate.

Dichotomous secondary outcomes (participants opting out of emails or with emails that bounce back) will be analyzed as described for the primary outcome. Total number of times the SAR was accessed and number of calls to CCO will be analyzed using Poisson regression with the natural log of the number of person-months as an offset term. For these models, the effect of each intervention factor will be expressed as a rate ratio with 95% confidence interval. In the event of significant overdispersion as assessed by a Lagrange multiplier test, a negative binomial distribution will be specified. For physician adherence to cancer screening guidelines, the dependent variable will be the number of eligible patients who meet a set of cancer-specific guidelines out of the total number of eligible patients listed to that provider and analyzed using logistic regression.

We had no a priori hypotheses about the interactions between the BCTs tested (anticipated regret, material incentive [behavior], and problem solving). Secondary analyses will include all 2-way interaction terms between experimental factors as well as comparison across the 8 experimental conditions. Secondary analyses will examine differences across subgroups defined by physician characteristics (eg, sex, years in practice, baseline screening rates, practice size, history of SAR use) and practice characteristics (eg, size of group, rurality, payment model). The length of the emails will also be explored as a potential effect modifier.

All analyses will be conducted in SAS version 9.4 (SAS Institute Inc) with statistical significance assessed at the 5% level.

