**Subgroup analyses**		
	History of SAR use	PEM physicians who have never logged in, those who have not logged in for 1 year but did previously, and those with 1 or >1 log-ins in the year prior to the trial
	Baseline cancer screening rate: breast (pretrial)	Proportion of enrolled, eligible patients who are up to date with breast screening at the physician level as of March 31, 2017
	Baseline cancer screening rate: cervical (pretrial)	Proportion of enrolled, eligible patients who are up to date with cervical screening at the physician level as of March 31, 2017
	Baseline cancer screening rate: colon (pretrial)	Proportion of enrolled, eligible patients who are up to date with colorectal tests intended for screening at the physician level as of March 31, 2017
	Sex	Sex of physician
	Years in practice	From the year of graduation
	Practice size	Number of patients enrolled to the physician’s practice
	Size of group	The total number of physicians belonging to the group and practicing within the LHIN^e^ Note: physicians who are part of the physician enrollment model group but practicing in another LHIN will not be included in this count
	Payment model	Identifies the specific type (ie, fee-for-service or capitation)
	Rurality	According to postal code of the PEM physician’s primary practice

^a^SAR: Screening Activity Report.

^b^PEM: physician enrollment model.

^c^FOBT: fecal occult blood test.

^d^CCO: Cancer Care Ontario.

^e^LHIN: Local Health Integration Network.

For testing each experimental factor, a sample size of 5576 physicians achieves 95% power to detect an absolute difference of 4% in SAR use (between those with the factor present versus those with the factor absent) using a 2-sided test at the 5% level of significance assuming a control arm proportion of 0.20 (estimated based on prior CCO data). We would consider small differences in proportions of primary care providers accessing the SAR to be clinically important. For example, if an intervention component resulted in only 4% more primary care providers accessing the SAR (ie, 223 more primary care providers) and if each of those primary care providers identified only a few patients overdue for screening, this would result in cancer screening for an additional 500 to 600 Ontarians.

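### History of SAR use, the only covariate named for the primary model, has two different codings in the article, and the model sentence does not say which applies

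*Protocol article*

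**What the plan says.** The Statistical Analyses section uses the variable twice. In the sentence on which characteristics will be described across conditions it is "their history of SAR use (previous use/no previous use", which is two levels. In the next paragraph, on the primary logistic regression, the text reads "The model will adjust for history of SAR use as a fixed covariate". No coding is attached there, and no other covariate is named.

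Table 3, in its block for subgroup analyses, defines the same-named variable differently. It lists "PEM physicians who have never logged in, those who have not logged in for 1 year but did previously" and then "those with 1 or >1 log-ins in the year prior to the trial". That is three levels if the last phrase means any log-in in the prior year, and four if one log-in and more than one are kept apart.

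The Data Collection and Outcomes section gives Table 3 a general role: "Table 3 details the variables to be collected and used in analysis". It defines the primary outcome as "whether or not the primary care physician accessed the SAR at least once between May and August 2017".

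**The concern.** Someone reading only the Statistical Analyses section would carry the yes/no gloss forward to the model, since it is the only definition given there. Someone following the pointer to Table 3 would fit recency and frequency categories. Both would be following the article, and they would fit different primary models.

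Two things depend on this. First, an odds ratio from logistic regression is conditional on the covariates in the model, so its size changes with the coding even under perfect randomization. Leaving the coding open leaves an analyst's choice in the primary estimate. Second, yes/no groups a physician who has not logged in for a year with one who logs in repeatedly. If those physicians differ in their chance of logging in over the next four months, which is plausible but not documented, the coarser coding discards information that is already being collected.

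**Working it through.** **1. The plan's own figure.** The inputs, from Power Calculation, are 5576 physicians (about 2788 per factor level), 20% versus 24%, and two-sided 5%.

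- Critical difference: 1.96 × √(2 × 0.22 × 0.78 / 2788) = 0.02175
- Standard error under the alternative: √((0.20 × 0.80 + 0.24 × 0.76) / 2788) = 0.01108
- Power: Φ((0.04 − 0.02175) / 0.01108) = Φ(1.647) = 95.02%

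The stated 95% reproduces. It comes from an unadjusted comparison, so it does not depend on how SAR history is coded.

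**2. What must be assumed.** The article gives neither the share of physicians in each history category nor their access rates. Both are assumed below, with overall access near 20%. Categories are ordered never / lapsed / log-in in the prior year, with the last split into 1 and >1 where four values are shown.

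**3. Method.** Let the shares be w_k, the access rates with the factor off be p_k, and the overall rate be m = Σ w_k p_k.

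- A common conditional log odds ratio b is found such that Σ w_k expit(logit p_k + b) = m + D, with D = 0.04 or 0.03.
- For a given grouping into strata with n_k = 5576 × share, stratum difference d_k and mean rate p̄_k: z = Σ(n_k/4)d_k / √(Σ(n_k/4) p̄_k(1 − p̄_k)), and power = Φ(z − 1.96).
- Variance explained by a grouping is Σ w_k(p_k − m)² / (m(1 − m)), with rates pooled inside each group.

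**4. One mix in full.** Shares are 30/30/20/20% and access rates 3/8/27/57%.

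- m = 0.009 + 0.024 + 0.054 + 0.114 = 0.201, and m(1 − m) = 0.1606
- Pooled rate among ever-users: 0.192 / 0.70 = 0.274
- Yes/no: (0.3 × 0.171² + 0.7 × 0.0733²) / 0.1606 = 0.078
- Four levels: (0.3 × 0.171² + 0.3 × 0.121² + 0.2 × 0.069² + 0.2 × 0.369²) / 0.1606 = 0.257
- Yes/no keeps 0.078 / 0.257 = 30% of the explained variance
- Power at 4 points: 94.9% unadjusted, 96.4% yes/no (z = 3.76), 98.8% four levels (z = 4.21)
- Power at 3 points: 77.7%, 81.2% and 88.9%; with three levels, 86.6%
- Odds ratio (factor on versus off) at 4 points: 1.26 unadjusted, 1.29 yes/no, 1.38 four levels

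A simulation of 1000 trials under this mix agrees. Power was 94.7%, 96.2% and 98.7% at 4 points and 76.5%, 80.0% and 88.4% at 3 points. Mean odds ratios at 4 points were 1.26, 1.29 and 1.37.

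**5. The range.**

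| Shares (%) | Access (%) | Kept by yes/no | Power at 4 points, yes/no → finer | Power at 3 points, yes/no → finer |
|---|---|---|---|---|
| 30/40/30 | 5/8/51 | 23% | 96.1 → 98.8 | 80.5 → 89.1 |
| 40/30/30 | 5/10/50 | 38% | 96.7 → 98.7 | 81.9 → 88.5 |
| 50/20/30 | 4/10/53 | 53% | 97.8 → 99.2 | 85.0 → 90.9 |
| 20/40/40 | 4/10/38 | 29% | 95.8 → 97.4 | 79.6 → 83.9 |
| 20/40/20/20 | 4/8/24/56 | 17% | 95.8 → 98.5 | 79.6 → 87.8 |
| 40/25/15/20 | 4/10/27/60 | 38% | 96.9 → 99.0 | 82.4 → 89.8 |
| 60/10/10/20 | 4/15/30/65 | 66% | 98.7 → 99.5 | 88.4 → 93.0 |
| 60/10/30 | 5/20/50 | 83% | 98.4 → 98.8 | 87.2 → 88.9 |
| 10/50/40 | 5/8/38 | 11% | 95.5 → 97.6 | 78.9 → 84.4 |
| 30/30/20/20 | 3/8/27/57 | 30% | 96.4 → 98.8 | 81.2 → 88.9 |
| 60/10/15/15 | 8/15/35/45 | 74% | 97.6 → 98.1 | 84.7 → 86.2 |

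The finer coding gains about 0.4 to 3 points of power at a 4-point effect and about 1.5 to 8.6 points at a 3-point effect. Yes/no keeps 11% to 83% of the explained variance, and less than half in 7 of the 11 mixes.

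**The case against.** The strongest reply is that the article never says the model uses yes/no. The two-level gloss belongs to the baseline description, the Table 3 entry sits under subgroup analyses, and neither is expressly tied to the model. This is correct. A reader might infer that the primary model adjusts for a dichotomy and so wastes most of the covariate's prognostic value. The documents support neither step: the model's coding is open, and the loss depends wholly on assumed category sizes and access rates. When most physicians have never logged in, the assumed mixes show yes/no keeping well over half.

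It can also be said that allocation is randomized, so the coding of a baseline covariate cannot bias the factor effects, and that power at the planned effect is at least 95% with either coding. Both statements stand. The larger gains occur only below the planned effect. They are not irrelevant, because the Power Calculation section says small differences would matter, but 3 points is not the design value.

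Finally, exact covariate coding is often left to the analysis plan. That would answer a missing definition. Here the article gives two definitions that disagree, so a reader cannot tell which one any fuller document should follow.

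**Conclusion.** The point holds as a conflict between two stated definitions of the only covariate named for the primary model. This part needs no assumed figure. The consequence is an unfixed choice that moves the conditional odds ratio (from 1.29 to 1.38 in the mix worked in full) and, if yes/no were chosen, a possible loss of precision. The size of that loss rests on assumed mixes and a common conditional odds ratio. It is small at the planned 4-point effect and moderate at 3 points. There is no bias, and the 95% power statement is right. The point is worth correcting because the correction is almost free, not because the trial's validity is at risk.

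**What to change.** Before analysis begins, state that the primary model, and every other model adjusting for history of SAR use, takes the Table 3 recency and frequency categories in place of yes/no. State whether one log-in and more than one log-in in the prior year are separate levels (four in all) or a single level (three in all). Use the same definition in the baseline table and the subgroup analyses.

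The data are already to be collected, so the cost is a sentence or two of text. Yes/no uses one degree of freedom, three levels use two and four levels use three, so the change takes one or two more out of 5576 observations. The Results section says that data cleaning and analysis had not begun when the article was submitted, so at that stage the choice could still be made without knowledge of the results.

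### With factors coded +1 and −1, the logistic coefficient is half the on-versus-off log-odds difference, but the protocol describes it as the whole difference

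*Protocol article*

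**What the plan says.** All of this is in the Statistical Analyses section of the protocol article, except the planning values.

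- **Coding.** The primary outcome, any SAR access over the four months, is analysed by logistic regression "using effect coding where +1 indicates the presence and –1 the absence of each factor".
- **Meaning of the coefficient, in general.** "With effect coding, the regression coefficient represents the difference in the mean response across all experimental conditions with that factor turned on", compared with the mean over the conditions with the factor off.
- **Meaning of the coefficient, by example.** "the regression coefficient for “anticipated regret” will represent the difference in the log-odds of accessing the SAR for providers allocated to conditions" 2, 5, 6 and 8, compared with conditions 1, 3, 4 and 7. These two sets match Table 2.
- **Reporting.** "The effect of each intervention factor will be expressed as an odds ratio with 95% confidence interval". For the count outcomes, "the effect of each intervention factor will be expressed as a rate ratio with 95% confidence interval".
- **Covariate.** "The model will adjust for history of SAR use as a fixed covariate".
- **Planning values.** Under Power Calculation, the fixed sample of 5576 physicians "achieves 95% power to detect an absolute difference of 4% in SAR use" for each factor, with a control proportion of 0.20 and a two-sided 5% test.

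The opt-out and bounce-back outcomes are to be analysed in the same way as the primary outcome. All two-way interactions between factors are planned as secondary analyses.

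**The concern.** The coding and the stated meaning of the coefficient cannot both hold. A logistic coefficient is the change in log-odds per one unit of the variable. Moving a factor from off (−1) to on (+1) is a change of two units, so the on-versus-off difference is twice the coefficient.

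The only link the article gives between the fitted coefficient and the odds ratio is the description of the coefficient as the full log-odds difference. An analyst who relies on it would exponentiate the coefficient and report an effect at half its size on the log scale, with an interval that is also too narrow and too close to 1. This would touch the primary estimate for all three factors.

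Size matters in this trial. Its stated aim is to learn which techniques work best, and the protocol treats small absolute differences as important, with 4 points as its example. The tests would look normal, because halving the coefficient also halves its standard error.

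**Working it through.** **Inputs.** Coding +1/−1 (Statistical Analyses); 5576 physicians, 20% versus 24%, two-sided 5% (Power Calculation). Assumption: simple randomization gives equal groups, so 5576/2 = 2788 per factor level and 5576/8 = 697 per condition.

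**1. The plan's own figure.**
- Pooled proportion 0.22; standard error under no difference √(2 × 0.22 × 0.78/2788) = 0.01110.
- Standard error under 20% versus 24%: √((0.20 × 0.80 + 0.24 × 0.76)/2788) = 0.01108.
- z = (0.04 − 1.96 × 0.01110)/0.01108 ≈ 1.65, so power = 0.950.

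The stated 95% reproduces. It compares two proportions and does not depend on how the factors are coded.

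**2. The coding.** With x = +1 or −1 and the other terms held fixed,

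logit(on) − logit(off) = β(+1) − β(−1) = 2β.

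So β is half the log odds ratio, exp(β) = √OR and exp(2β) = OR.

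**3. At the planning values.**
- OR = (0.24/0.76)/(0.20/0.80) = 1.263; log OR = 0.2336.
- β = 0.2336/2 = 0.1168.
- SE of the log OR = √(1/(2788 × 0.20 × 0.80) + 1/(2788 × 0.24 × 0.76)) = 0.0649, so SE(β) = 0.0324.

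| Quantity | Value | 95% CI |
|---|---|---|
| exp(β), the coefficient taken as described | 1.124 | 1.055 to 1.198 |
| exp(2β), the on-versus-off odds ratio | 1.263 | 1.112 to 1.434 |

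**4. On the absolute scale.** Odds of 0.25 × 1.124 = 0.281 correspond to 0.281/1.281 = 21.9%. A true 4-point difference would read as about 1.9 points.

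**5. Model fits.** Logistic models were fitted to the expected counts for the eight conditions (697 each, one factor active at 20% versus 24%). Under +1/−1 coding β was 0.1168 in every fit, with or without the two-way interactions and with or without a history covariate (assumed binary, evenly split, log-odds 1.5 apart). Under 0/1 coding the main-effects coefficient was 0.2336. The Wald z in the main-effects model without the covariate was 3.60 under both codings, so p-values do not change.

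**6. Interactions.** If γ multiplies the product of two +1/−1 factors, the difference in differences of log-odds is (γ + γ) − (−γ − γ) = 4γ.

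**The case against.** The strongest reply is that the article never writes the odds ratio as exp(β). The sentence on reporting has the effect of the factor as its subject, not the coefficient, and the intended contrast is named without ambiguity by its study arms. An odds ratio requested for that contrast from a classification factor with effect parameterization would come out as exp(2β), which is correct. The article names SAS 9.4 but no procedure or syntax.

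This stands as a limit on the consequence. A reader might infer that the trial's odds ratios and rate ratios will all be wrong. The documents do not support that: the outcome depends on the implementation, and the error follows only if the coefficient is exponentiated directly. The reply does not rescue the description itself, which is false under the stated coding and is corrected nowhere else in the article. Condensation can explain an omission, but not an incorrect definition.

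Three further limits also stand.
- **Secondary models.** The primary method is carried over explicitly only to opt-out and bounce-back. For the count and guideline-adherence models neither the coding nor the meaning of a coefficient is restated.
- **Interactions.** The article gives no interpretation of an interaction coefficient, so there is no misstatement there.
- **Detectability.** A halved estimate would not necessarily pass unnoticed. The planned comparison across the eight conditions could expose it, since an odds ratio of 1.124 would sit badly beside access rates near 20% and 24%.

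**Conclusion.** The point holds as a wrong stated rule for interpreting the primary model: under +1/−1 coding the coefficient is half the on-versus-off log-odds difference. This is algebra and rests on no assumption about the data. Adjusting for SAR history makes the odds ratio conditional on that covariate but leaves the factor of two unchanged.

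The damage to reported results is conditional. If the coefficient is exponentiated directly, each odds ratio and each confidence limit becomes its own square root. The size shown above assumes the protocol's 20% versus 24% and equal allocation. The same applies to opt-out and bounce-back, and to the count and adherence models if they share the coding. The design, the intended contrast, the tests and the 95% power are sound.

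**What to change.** Replace the description of the coefficient in Statistical Analyses. Either change is enough:

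- **Keep +1/−1.** State that the coefficient is half the on-versus-off difference in log-odds, that the odds ratio (or rate ratio) is exp(2β), and that its confidence limits are exp(2(β ± 1.96 SE)).
- **Code +0.5/−0.5.** The coefficient is then the full difference and can be exponentiated directly.

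State which coding the count and adherence models use. If +1/−1 is kept in the two-way interaction models, add that the ratio of odds ratios is exp(4β) of the interaction coefficient.

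Moving to 0/1 coding is not an equivalent repair once interactions are in the model. The factor's coefficient then becomes its effect with the other factors off, and in the fits above (without the covariate) its z fell from 3.60 to 2.08.

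The cost is one or two sentences and a contrast statement in the program. The sample, the main-effect tests and the power are unchanged, and the article reports that analysis had not begun when it was submitted.
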